The OMOP CDM standard includes the representation of clinical content using standardized vocabularies, enabling the mapping of primary data from various data standards (eg, International Classification of Diseases, 10th Revision [ICD-10] and German Procedure Classification System [OPS]) and facilitating conversion to modern data ontologies such as SNOMED-CT (Systematized Nomenclature of Medicine—Clinical Terminology) and/or LOINC (Logical Observation Identifiers Names and Codes). Furthermore, OMOP CDM supports the eventual integration into the developing research data infrastructure of the Medical Faculty at Ruhr University Bochum, potentially using Health Level Seven Fast Healthcare Interoperability Resources (HL7 FHIR) profiles. This infrastructure constitutes the integration pathway for clinical deployment. Clinical input data (eg, demographics, vital signs, laboratory values, medications, and delirium assessments) are captured automatically from the Hospital Information System, Patient Data Management System, and Anesthesia Information Management System without additional manual data entry by clinical staff, and risk predictions are generated automatically within existing workflows at the point of care. For the preoperative clinical model, all input variables are documented as part of standard preanesthesia assessment, and no laboratory analyses are required, meaning a risk prediction is available immediately at the time of the outpatient consultation with no analytical turnaround time. For the integrative postoperative model, predictions are updated automatically as new data are entered into the electronic record, ensuring timely availability for clinical decision-making throughout the hospital stay.

The processed clinical data will then be combined with data from subsequent work packages to support the development of an artificial intelligence (AI) model. Individual deidentified participant data (including the data dictionary), statistical code, and any other materials will be accessible to authorized personnel of the AI Center.

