Given the limited sample size relative to the high-dimensional omics data, all predictive models are exploratory and hypothesis-generating. External validation in independent cohorts will be necessary to confirm predictive performance and clinical utility. Models trained on clinical variables alone will be benchmarked alongside multiomics models for exploratory comparison, reflecting potential applicability in settings where omics data are not routinely available.

The final operating threshold will be selected to prioritize either sensitivity (screening scenario) or specificity (confirmatory setting), as dictated by the clinical use case. Alongside the integrative models, versions limited to routinely available clinical variables will be trained and benchmarked to ensure bedside applicability where omics data are not regularly available. To interpret the resulting models, feature-attribution techniques such as SHAP (Shapley Additive Explanations) values will quantify and visualize each variable’s influence on the prediction, thereby generating mechanistic hypotheses about the molecular and functional pathways leading to POD. To clarify the clinical deployment strategy, the study is designed to yield 2 distinct and complementary model types. The first is a purely preoperative clinical model, trained exclusively on variables available at the preanesthesia outpatient clinic, specifically the DRAS, Mini-Mental State Examination score, age, comorbidities, surgical type, and medication profile. This model requires no blood sampling and can generate a risk prediction at the time of the outpatient consultation, typically days to weeks before surgery. This is the primary bedside instrument of the study and the relevant window for initiating preventive measures, including medication review and reduction of anticholinergic burden, sleep hygiene counseling, optimization of sensory aids, cognitive stimulation, and planning of early postoperative mobilization. The second is an integrative multimodal model incorporating longitudinal biomarker data from all 4 perioperative collection time points. This model serves a distinct purpose: continuous refinement of risk estimates throughout the hospital stay, enabling early detection of evolving POD in the postoperative period. Postoperative biomarker data are therefore not a prerequisite for preoperative risk stratification but an additional layer extending clinical utility into the postoperative setting.

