## Results

### Overview

The study was registered in the German Clinical Trials Register (DRKS00033854) on March 18, 2024. Patient recruitment commenced in January 2024 and is ongoing at the time of manuscript submission (Table 2). As of now, 135 of the approximately planned 200 to 300 patients have been enrolled, corresponding to approximately two-thirds of the target sample size. Sample collection and laboratory analyses are ongoing. Enrollment is proceeding according to the projected timeline (Table 1), and no major protocol deviations have occurred to date. The first results are expected in July 2026.

**Table 2. T2:** Timeline of the study.

Item	Details
Initial ethical approval	Approved in May 2023
Funding date	Funded in January 2023
Ethical approval amendment	Approved in March 2024
Trial registration	Registered in the German Clinical Trials Register (DRKS00033854) on March 18, 2024
Start of recruitment	Recruitment started in January 2024
End of recruitment	Recruitment is expected to be completed in December 2026
Sample size status	As of February 2026, a total of 135 participants have been enrolled
Data collection period	Data collection is planned from April 2024 to March 2027
Laboratory analyses	Laboratory analyses commenced in February 2026
Statistical analysis	Statistical analysis is scheduled to begin in July 2026
Expected publication	First results are expected to be published in Spring 2027

Biospecimen collection at all 4 predefined perioperative time points is ongoing. Sample processing, including initial proteomic and transcriptomic preparation steps, has been initiated in parallel with recruitment to ensure standardized handling and storage conditions. Comprehensive laboratory analyses are currently underway.

Data cleaning and database validation procedures are being performed continuously. Final data lock is anticipated after the completion of recruitment. Statistical analyses, including integrative multiomics evaluation and the development of predictive models, began in January 2026. First results are expected in March 2026, with dissemination through peer-reviewed publications planned thereafter.

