### Trial Status

The first patient was recruited on January 15, 2024. The inclusion of participants is ongoing and is expected to continue until November 2026. The first results are expected in July 2026. The trial protocol and statistical analysis plan can be accessed through the corresponding author.

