Future directions should focus on improving the interpretability of AI models, integrating them into clinical workflows, and considering ethical aspects. Collaborative efforts between data scientists, clinicians, and researchers are essential to validate AI-driven predictive models and ensure their successful application in clinical settings. By overcoming these challenges, AI has the potential to significantly improve the accuracy of POD prediction and facilitate personalized interventions, ultimately improving patient outcomes and reducing the burden of POD. With regard to cost-effectiveness, a formal health-economic analysis lies beyond the scope of this protocol study, but several considerations are relevant. First, the preoperative clinical model relies exclusively on routinely collected clinical data and requires no additional laboratory analyses, thereby incurring no additional diagnostic costs. Second, POD is associated with a well-documented economic burden, including prolonged hospitalization, higher rates of institutionalization, extended mechanical ventilation, and long-term cognitive decline. Targeted nonpharmacological prophylaxis initiated following early identification of high-risk patients has been shown in randomized trials to reduce POD incidence and shorten hospital stays, yielding downstream cost savings that are likely to outweigh the costs of screening. Third, the full proteomic and transcriptomic workup performed in this study is explicitly designed to identify a focused panel of high-yield biomarkers, which is anticipated to inform the development of targeted, lower-cost point-of-care assays for future routine clinical implementation, substantially reducing per-patient costs relative to the comprehensive analytical workup performed during the study phase.

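### The integrative model's in-stay timeliness and early-detection claims are not supported for its omics inputs, which have no stated turnaround or route into the electronic record

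*Protocol article*

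**What the plan says.** The article (Integrative Data Analysis and AI Model Development) describes two model types. One is a preoperative clinical model. The other is an "integrative multimodal model incorporating longitudinal biomarker data from all 4 perioperative collection time points", whose purpose is "continuous refinement of risk estimates throughout the hospital stay, enabling early detection of evolving POD in the postoperative period".

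Clinical Data Collection and Processing then describes deployment. "Clinical input data (eg, demographics, vital signs, laboratory values, medications, and delirium assessments) are captured automatically" from three hospital systems. For the preoperative model, "a risk prediction is available immediately at the time of the outpatient consultation with no analytical turnaround time". For the integrative model, "predictions are updated automatically as new data are entered into the electronic record, ensuring timely availability for clinical decision-making throughout the hospital stay".

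On dates, Trial Status says "The first patient was recruited on January 15, 2024", and Table 2 says "Laboratory analyses commenced in February 2026". Strengths and Limitations says that the full omics workup is meant to find a focused panel, "which is anticipated to inform the development of targeted, lower-cost point-of-care assays for future routine clinical implementation".

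**The concern.** The integrative model differs from the clinical one through its molecular layers: mass-spectrometry proteomics of plasma and cell fractions, RNA microarrays, bisulfite-based methylation and ELISA. The timeliness sentence depends on data arriving in the electronic record, but the inputs listed as arriving there automatically are clinical. The article addresses analytical turnaround for the model that needs no laboratory work and does not address it for the model that does.

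At stake is what the study may conclude. If the multiomics model's discrimination is reported under an in-stay early-detection label, readers will take it as the performance of something that could run at the bedside. A version restricted to results that exist during the stay is a different model, and its performance may be lower. This concerns only when a result exists; it does not suggest that predictions alter care in this cohort.

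**Working it through.** The article gives no omics turnaround, so there is no stated figure to reproduce. The check sets the passages side by side, does the date arithmetic, and then illustrates what a turnaround would do.

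**1. Claim against described inputs**

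- Claimed: predictions in time for decisions throughout the stay, and early detection from biomarkers at four draws.
- Described as captured automatically: demographics, vital signs, laboratory values, medications and delirium assessments, given as examples. No omics result is among them.
- The same section says that the processed clinical data are combined afterwards with data from later work packages.
- Blood Sampling and Analysis describes a stepwise discovery process. Polymorphisms are selected after in silico work on the identified genes, and the identified genes and proteins are quantified as a last step. Part of the input list is therefore not defined until discovery is complete.

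**2. Delay from the earliest samples to the start of laboratory analyses** (days / 30.4375)

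- From 15 January 2024 (first patient) to 1 February 2026: 748 days, 748 / 30.4375 = 24.6 months. To 28 February 2026: 775 / 30.4375 = 25.5 months.
- Table 2 also dates data collection from April 2024. From 30 April 2024 to 1 February 2026: 642 / 30.4375 = 21.1 months. From 1 April 2024 to 28 February 2026: 698 / 30.4375 = 22.9 months.

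The gap is thus about 21 to 25 months for the earliest samples and shorter for later patients. February 2026 is only the start of assays, so some samples will wait longer than this. By then 135 patients were enrolled, which is 135/300 = 45% to 135/200 = 67.5% of the planned 200 to 300. Only sample processing and initial preparation steps are said to have run alongside recruitment. Practically none of these 135 could have had an omics result during the stay.

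**3. Effect of a turnaround in use (assumed 24 to 48 hours; not in the document)**

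Result day = draw day + turnaround. Days left = 5 − result day + 1, with a minimum of 0, counted against the five daily nurse assessments. This count is generous, since it includes the result day itself. The preoperative draw is set at day 0 at the latest.

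| Draw | Result day (24 h / 48 h) | Assessment days left (24 h / 48 h) |
|---|---|---|
| Preoperative, day 0 | 1 / 2 | 5 / 4 |
| Immediately postoperative, day 0 | 1 / 2 | 5 / 4 |
| Day 2 | 3 / 4 | 3 / 2 |
| Last draw, day 4 (Table 1) | 5 / 6 | 1 / 0 |
| Last draw, day 5 (text) | 6 / 7 | 0 / 0 |

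Table 1 places microarray and methylation work at baseline and recovery room only, and genotyping at baseline only. The late rows therefore bear mainly on proteomics and ELISA. Table 1 also ticks delirium screening at discharge, so a later result is not worthless for a patient still in hospital after day 5.

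**The case against.** The strongest reply is that the gap of about two years measures the wrong thing. Banking samples and assaying them in batches is normal in a development cohort and says nothing about turnaround in use. The timeliness sentence stands in a description of a deployment pathway, so the absence of in-stay results for the 135 patients contradicts no stated claim about them. This stands. A reader might infer from the delay that the design cannot show anything about early detection. The documents do not support that, because samples drawn before onset can still show whether the signal was there.

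A reader might also infer that the analysis will treat each biomarker as known at the draw. The article does not say so. It fixes no prediction time for this model, and that detail may sit in the analysis plan.

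Three further points have weight. The article already plans versions limited to routine clinical variables and names the preoperative model as its main bedside tool. It calls all models exploratory and asks for external validation of clinical utility. The dating is also not firm: the Overview text has integrative analyses beginning in January 2026, before Table 2's start of laboratory work, and the storage sentence covers only remaining samples. A shift of a month changes nothing here.

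What this reply leaves untouched is the affirmative wording. The exploratory caveat concerns sample size and generalisability. External validation that ignored assay turnaround would not establish availability either. The article does not say which time points the routine-variable versions cover, and it attaches the in-stay claim to the integrative model.

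**Conclusion.** The point holds in limited form. The article asserts timely in-stay availability and early detection for a model whose defining inputs have no stated turnaround and no described route into the electronic record, and it defers fast assays to later development. The clinical inputs of the same model can update during the stay, so the defect is confined to the omics layers. The study can show that a draw carried information before POD onset. It cannot show that a prediction using that information would have been available.

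The 21 to 25 months rests on the article's own dates, for the earliest samples only, and should not be read as turnaround in use. The day-by-day table rests on an assumed 24 to 48 hours. On that assumption the two earliest draws keep 4 to 5 of the five assessment days, the day-2 draw keeps 2 to 3, and the last draw keeps 0 or 1. The correction is worth making because it changes what may be concluded, but it does not undermine the study's discovery aims.

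**What to change.** 1. In Clinical Data Collection and Processing and in Integrative Data Analysis and AI Model Development, limit the timeliness and early-detection wording to inputs that have a result during the stay. Use the routine-clinical-variable versions already planned, updated through the stay, as the in-stay model.
2. For any in-stay claim that includes biomarkers, state an assumed turnaround for each assay, let each biomarker enter at draw time plus that turnaround, count only POD with later onset, and show results over a range of turnarounds.
3. Report the full multiomics model as retrospective biomarker discovery that feeds the targeted assays described in Strengths and Limitations.

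The cost is wording in the protocol and analysis plan, plus an added evaluation on data already being collected. No new samples are needed. The downside is that the performance quoted for in-stay use will probably be less favourable.

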### Integrative Data Analysis and AI Model Development

This section describes the planned integration and analysis of clinical and multiomics data for the exploratory investigation of potential predictors of POD. Data will be analyzed both independently and in combination with a focus on patient groups with and without POD. Prior to analysis, clinical datasets will be preprocessed; for example, variables with more than 30% missingness will be discarded, whereas remaining gaps will be imputed, where applicable, when missing at random, using multiple imputation by chained equations or other suitable methods. Clinical continuous variables will be centered and scaled to *z* scores, and categorical variables will be one-hot encoded. In proteomics, the analysis will involve deriving accurate quantitative protein data from peptide data, particularly by improving the utilization of shared peptides found in multiple proteins.

Univariate analyses, such as *t* tests and ANOVA (with adjustments for multiple comparisons), will be applied to identify candidate features, which may subsequently be subjected to pathway and enrichment analyses to generate mechanistic hypotheses regarding molecular processes potentially involved in POD. Multivariate techniques, including principal component analysis and clustering, will be applied to uncover latent patient phenotypes beyond a priori groupings.

The significant findings from clinical and omics data are fed into a knowledge base for targeted searches, facilitating focused investigations (targeted proteomics). The entire dataset is also analyzed using multivariate methods, including principal component analysis and clustering, to reveal latent patient phenotypes beyond a priori groupings. Supervised prediction of POD will rely on a benchmark suite of algorithms (eg, regularized logistic regression, random forests, support vector machines, and gradient-boosting methods). Model training and hyperparameter tuning will follow a nested cross-validation scheme, supplemented by a temporally separated holdout set when sufficient data are available. Discrimination and calibration will be reported with area under the receiver operating characteristic curve, area under the precision-recall curve, sensitivity, specificity, accuracy, and *F*-score. The final modeling protocol will be chosen on the basis of performance, interpretability, and clinical plausibility and can be iteratively updated as additional data accumulate.

Given the limited sample size relative to the high-dimensional omics data, all predictive models are exploratory and hypothesis-generating. External validation in independent cohorts will be necessary to confirm predictive performance and clinical utility. Models trained on clinical variables alone will be benchmarked alongside multiomics models for exploratory comparison, reflecting potential applicability in settings where omics data are not routinely available.

The final operating threshold will be selected to prioritize either sensitivity (screening scenario) or specificity (confirmatory setting), as dictated by the clinical use case. Alongside the integrative models, versions limited to routinely available clinical variables will be trained and benchmarked to ensure bedside applicability where omics data are not regularly available. To interpret the resulting models, feature-attribution techniques such as SHAP (Shapley Additive Explanations) values will quantify and visualize each variable’s influence on the prediction, thereby generating mechanistic hypotheses about the molecular and functional pathways leading to POD. To clarify the clinical deployment strategy, the study is designed to yield 2 distinct and complementary model types. The first is a purely preoperative clinical model, trained exclusively on variables available at the preanesthesia outpatient clinic, specifically the DRAS, Mini-Mental State Examination score, age, comorbidities, surgical type, and medication profile. This model requires no blood sampling and can generate a risk prediction at the time of the outpatient consultation, typically days to weeks before surgery. This is the primary bedside instrument of the study and the relevant window for initiating preventive measures, including medication review and reduction of anticholinergic burden, sleep hygiene counseling, optimization of sensory aids, cognitive stimulation, and planning of early postoperative mobilization. The second is an integrative multimodal model incorporating longitudinal biomarker data from all 4 perioperative collection time points. This model serves a distinct purpose: continuous refinement of risk estimates throughout the hospital stay, enabling early detection of evolving POD in the postoperative period. Postoperative biomarker data are therefore not a prerequisite for preoperative risk stratification but an additional layer extending clinical utility into the postoperative setting.

